### Statistical analysis

#### Primary analyses

Significant differences at baseline between the conditions will be checked by performing one-way ANOVA’s and chi-square tests.

Effects of the intervention on all outcomes will be assessed by performing intention-to-treat analyses using general linear mixed models. Baseline to post-intervention and 3- and 6-month follow-up differences will be used as repeated measures, with treatment (2 levels), time (3 levels) and their first-order interactions as fixed factors. Confidence intervals of 95% will be calculated for all outcomes. Drop-out and non-adherence are relatively common in online interventions [56]. Therefore, secondary analyses will be performed to examine effects on outcome variables for participants who adhered to the intervention (i.e., all session completed and self-reported minimum of 2 h per week spent on intervention). At post-intervention and follow-up, effect sizes (Cohen’s *d*) will be calculated using means and standard deviations. Effect sizes of 0.80 are considered large, effect sizes of 0.50 are evaluated as moderate, and effect sizes of 0.20 are considered small [57].

Initiative on Methods, Measurement, and Pain Assessment in Clinical Trials (IMMPACT) recommendations will be followed to evaluate the proportion of participants showing clinically significant change [58]. Clinical improvement will be assessed with missing values imputed by the Expectation Maximization-algorithm. Proportions of clinically improved participants and Chi-square tests will assess statistically significant differences in the proportions for the two conditions. It will be calculated for (a) pain interference (MPI – Interference), (b) pain intensity (NRS), and (c) CIPN symptom severity (EORTC QLQ – CIPN 20). A decrease of at least 0.6 standard deviation will be assessed as evidence of clinically significant change for the MPI – Interference scale, based on the IMMPACT guidelines [58]. Decreases of 20% or higher in pain intensity (NRS) will be assessed as minimum and moderate changes. No specific IMMPACT guidelines exist for the HADS. Therefore, a distribution-based decrease of at least 1 standard error of the mean is recommended [58].

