Even though online interventions are relatively new, several such interventions have demonstrable effectivity in improving QoL in cancer patients and survivors [28, 30–32]. A randomized controlled trial (RCT) has shown that the use of an online CBT intervention significantly improved CIPN pain intensity and may be effective [27]. Furthermore, research has shown that online interventions based on ACT are capable of improving pain intensity, pain interference, pain catastrophizing, disability, depression, anxiety, psychological inflexibility, and QoL in chronic pain patients with a variety of pain diagnoses (e.g., fibromyalgia, rheumatoid arthritis, and back complaints) [33, 34]. These findings suggest that an online self-help intervention based on ACT might be effective for adult cancer survivors with chronic painful CIPN as well. However, effects may differ between patients, since previous research has shown factors such as pain intensity, depressive and anxiety symptoms, and emotional well-being to predict the effectiveness of online ACT for chronic pain [35], and the extent to which patients benefit from the online intervention may hence vary. Furthermore, there may also be differences in the effectiveness with different types of the online intervention, namely with or without guidance. Earlier research has shown that guidance, including feedback, explanations, motivations and reminders, improves treatment effects compared to unguided interventions [36, 37]. The primary aim of this study researching the online intervention named ‘Embrace Pain’ is to reduce pain interference in cancer survivors with chronic painful CIPN. To study this, three objectives have been formulated:*Objective 1:* To examine the effectiveness of an online self-help intervention based on ACT for reducing pain interference in cancer survivors with chronic painful CIPN in a randomized controlled trial (RCT) and compare this to a waiting list condition (WLC).*Objective 2:* To examine which baseline demographic, clinical, and psychosocial factors may moderate the effectiveness of an online self-help intervention based on ACT.*Objective 3:* To examine the extent to which effects differ between guided and unguided versions of the online self-help intervention based on ACT.

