## Methods

### Study design

An RCT will be carried out with two parallel, non-blinded groups. Participants will be involved in the study for a duration of 8 months from the first to the last measurement. Outcome measures will be collected at baseline (T0), early-intervention (T1; 3 weeks after baseline), mid-intervention (T2; 6 weeks after baseline), directly at the end of intervention (T3; 2 months after baseline), and through two follow-up measurements (T4; 3 months after the intervention, T5; 6 months after intervention). A flowchart of the study is shown in Fig. 1.

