### Intervention

The experimental condition includes an online psychological intervention with therapist email guidance based on ACT. The intervention can be worked through by the patient from home or at another location of choice, in a webpage or app by logging in with an email and self-created password. Participants receive a welcome letter from the supervisor. It consists of 6 modules which can be worked through in 8 weeks. The intervention primarily consists of text and experiential exercises, complemented with illustrations, metaphors, and audio (mp3) files. Before starting the module, participants read an introduction about the training. The first module includes psychoeducation on neuropathic pain and CIPN (Table 1). Participants will be provided with information to familiarize themselves with intervention goals and mindfulness exercises central to ACT. In subsequent modules, participants will learn about the aversive effects of pain avoidance, gain insight into their personal values, and work on pain acceptance. Throughout the intervention, participants will exercise to recognize unhelpful thoughts about their pain and learn the difference between the subjective (judging) and objective self, create activities that align with values, and think about concrete actions to prevent relapse. When access to the online environment is terminated, participants can no longer view the online environment or communicate with the supervisor. However, participants can always continue to view the session they submitted.

**Table 1 Tab1:** Schematic overview of modules of the ACT intervention

Module	Therapeutic processes	Information	Assignments	Audio files (mindfulness)
Welcome		Online environment, contact, additional help, other long-term consequences, and tips.		
1: Chronic neuropathic pain	Psychoeducation	CIPN and chronic pain		A: Concentration on breathing
2: On the way to values	Values	Values and valued-based activities	I: Explore your values II: My values III (optional): My values in pictures	A: Body exploration
3: Away from my values	Pain avoidance	Avoidance and managing pain	I: My ways of avoiding II: Moment when I am in pain	A: Concentration on breathing B: Body exploration C: Three-minute breathing space
4: On the road with skills	Commitment and Defusion	Learning how to deal with pain differently	I: Acceptance in action II: Your recurring thoughts of pain III: Is the thought useful? IX (optional): Struggle or open up	A: Allowing what is

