### Waiting list condition

The control condition includes a WLC. At 5 months after start (i.e., T4) participants in the WLC receive the opportunity to follow the intervention without email guidance by a therapist. They neither receive a welcome letter at the start, which means that they only read the introduction about the training before starting.

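### The ACT-versus-waiting-list model includes month 8 (T5), three months after the waiting list is offered the unguided course, so T5 and any effect averaged over visits do not answer Objective 1

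*Protocol article*

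**What the plan says.** Objective 1 (Background) is to examine whether the online ACT course reduces pain interference, compared with a waiting list.

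Study design puts T3 at the end of the intervention, two months after baseline, and then adds "two follow-up measurements (T4; 3 months after the intervention, T5; 6 months after intervention". It also states: "Participants will be involved in the study for a duration of 8 months from the first to the last measurement".

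The section Waiting list condition says: "At 5 months after start (i.e., T4) participants in the WLC receive the opportunity to follow the intervention without email guidance". These participants do not get the welcome letter either. On the length of the course, the Intervention section says: "It consists of 6 modules which can be worked through in 8 weeks".

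Primary analyses specifies an intention-to-treat mixed model: "Baseline to post-intervention and 3- and 6-month follow-up differences will be used as repeated measures". The fixed factors are treatment at two levels, time at three levels, and their interaction. Cohen's d is to be calculated at post-intervention and at follow-up. Nothing in this section treats the 6-month visit differently from the other two.

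**The concern.** The comparator named in Objective 1 exists only until T4. After that the control arm may be working through the course, yet T5 enters the model under the same two-level treatment factor as T3 and T4. One label then covers two different comparisons.

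What is at stake is interpretation. If the arms draw closer at T5, the model cannot tell whether the ACT arm lost its benefit or the waiting-list arm gained one. A T5 effect size reported as ACT against waiting list would carry the wrong name. A treatment effect pooled over the three visits would mix two estimands. A significant treatment-by-time interaction could arise from the control arm catching up.

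**Working it through.** **Timeline, from the article's own figures**

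- T3 = month 2 (Study design).
- T4 = 2 + 3 = month 5.
- T5 = 2 + 6 = month 8. This reproduces the stated 8 months of participation.
- WLC access opens at month 5, which the article itself equates with T4.
- Access before T5 = 8 - 5 = 3 months, about 13 weeks. The course takes 8 weeks, so a WLC participant who starts promptly can finish about 5 weeks before T5.

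**What each visit compares**

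| Visit | Month | ACT arm | WLC arm | Answers Objective 1? |
|---|---|---|---|---|
| T3 | 2 | guided course just ended | waiting | yes |
| T4 | 5 | 3 months after the course | waiting, if T4 is completed before access opens | yes, on that condition |
| T5 | 8 | 6 months after the course | offered the unguided course 3 months earlier | no |

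The three time levels match the three changes from baseline (to T3, T4 and T5), so T5 is one third of any equally weighted average over visits.

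**Size**

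Inputs:

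- d = 0.50 is the planning effect in Sample size calculation. It is assumed to hold at every visit against an untreated control.
- u is the share of the WLC arm that takes up the course.
- r is the effect of the unguided course relative to the guided one.

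The article gives neither u nor r, so both are assumptions shown over a range.

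Formulas:

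- T5 contrast = 0.50 × (1 - u × r)
- Three-visit average = (0.50 + 0.50 + T5 contrast) / 3
- Loss = 1 - average / 0.50

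| u | r | T5 contrast | Three-visit average | Loss in average |
|---|---|---|---|---|
| 0 | any | 0.50 | 0.50 | 0% |
| 0.25 | 0.50 | 0.44 | 0.48 | 4% |
| 0.50 | 0.50 | 0.375 | 0.458 | 8% |
| 0.50 | 0.75 | 0.31 | 0.44 | 12.5% |
| 0.75 | 0.75 | 0.22 | 0.41 | 19% |
| 1 | 1 | 0 | 0.33 | 33% |

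First non-trivial row in full: 0.50 × (1 - 0.25 × 0.50) = 0.4375; (0.50 + 0.50 + 0.4375) / 3 = 0.479; 1 - 0.479 / 0.50 = 0.042.

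**Why T5 cannot be interpreted by itself**

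A T5 contrast of 0.31 arises if the ACT benefit is fully maintained while half the WLC arm gains three quarters of the guided effect. It also arises if nobody in the WLC arm starts the course and the ACT benefit has faded from 0.50 to 0.31. The between-arm difference is the same in both cases.

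**With T5 left out**

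The average over T3 and T4 is (0.50 + 0.50) / 2 = 0.50, whatever u and r are.

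**The case against.** The strongest defence is that the model contains the treatment-by-time interaction and that effect sizes are calculated by visit. The T3 and T4 contrasts can therefore be read from it without contamination. That stands. A reader might infer that the whole primary analysis is diluted, but the article nowhere says that the averaged treatment effect is the efficacy test. The problem is confined to T5, to averages that include it, and to the joint interaction test.

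A second defence is intention-to-treat. The T5 comparison is still randomised and is valid as a comparison of two strategies. That stands too: it is mislabelled, not meaningless. Nor should one say that the WLC arm will have received the same treatment. It is offered the course, without guidance, and uptake may be low. The article itself calls drop-out and non-adherence relatively common online and plans for 30% drop-out. This is why the range above starts at 25% uptake. Some uptake is nevertheless expected, because Objective 3 needs WLC participants to take the unguided version.

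Third, if the delayed course helps, the T5 contrast shrinks. The risk is then a missed or misread late effect, not a false claim of benefit over a waiting list. That is correct, and it limits the harm.

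Two further inferences are tempting and are not supported. One is that three visits with no named primary contrast inflate the type I error. The article specifies one model and no rule that any single significant visit suffices, and a condensed article may leave the choice of contrast to the full plan. The other is that the plan already makes T4 its primary visit, because it calls pain interference at 3-month follow-up its indicator of treatment effect. That phrase belongs to the predictor analysis under Secondary analyses, not to Objective 1.

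None of this removes the core point: the article positively places a visit after WLC access opens in a model meant to compare ACT with a waiting list.

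**Conclusion.** The point holds in this limited form. The timing conflict follows from the article's own dates and needs no outside figure. At T5 the arms differ by immediate guided ACT against the offer of delayed unguided ACT, so quantities that use T5 do not estimate the effect named in Objective 1. T3 is unaffected, and T4 is unaffected provided it is completed before access opens.

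The size is conditional. It rests on a sustained d of 0.50, on equal weighting of the visits, and on assumed uptake and relative effect. Over the range shown, the T5 contrast runs from 0.44 down to 0 and the three-visit average loses about 4 to 33%. The upper end requires every WLC participant to take the course and to gain the full guided effect, so it is a bound and not an expectation. With no uptake there is no dilution.

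**What to change.** State that the ACT-versus-WLC test and its effect sizes rest on the T3 and T4 contrasts only. Either fit that model through T4, or keep T5 in the model and draw the Objective 1 inference from explicit contrasts at T3 and T4. Whether T3, T4 or their average carries the test is for the full plan to state; the article gives no ground for preferring one.

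State also that T4 questionnaires are completed before WLC access opens.

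Report T5 separately, either as immediate guided against delayed unguided ACT or as within-arm results (maintenance in the ACT arm, change after access in the WLC arm). Make no ACT-versus-waiting-list claim at T5.

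The cost is a change of analysis wording and one rule on the order of T4 data collection and WLC access. No extra participants or measurements are needed. What is given up is a 6-month efficacy claim against a waiting list, which this design cannot support once the WLC arm has access.

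### The primary model treats the 6-month follow-up (T5, month 8) as an ACT-versus-waiting-list visit, although the waiting list is offered the ACT course from month 5

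*Protocol article*

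**What the plan says.** Objective 1 (Protocol article, Background) is to study the effect of the online ACT course on pain interference and to "compare this to a waiting list condition (WLC").

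Study design fixes the visits: "directly at the end of intervention (T3; 2 months after baseline"), then "T4; 3 months after the intervention, T5; 6 months after intervention". The same section adds: "Participants will be involved in the study for a duration of 8 months from the first to the last measurement".

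The Waiting list condition section sets the point at which the control arm changes: "At 5 months after start (i.e., T4) participants in the WLC receive the opportunity to follow the intervention without email guidance by a therapist". The Intervention section gives 8 weeks for the six modules.

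Under Primary analyses, effects on all outcomes are assessed by "performing intention-to-treat analyses using general linear mixed models". The model is: "Baseline to post-intervention and 3- and 6-month follow-up differences will be used as repeated measures, with treatment (2 levels), time (3 levels". The interaction of treatment with time is also a fixed factor, and Cohen's d is calculated at post-intervention and at follow-up. Nothing in that section treats T5 differently from T3 and T4.

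**The concern.** A two-level treatment factor across three visits presumes that the control arm is the same condition at each visit. Here it is not: between the second and third modelled visits the control arm gains access to the treatment under test.

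Objective 3 compares guided with unguided ACT, and the waiting list is the only arm described as receiving the unguided form. The protocol thus relies on this arm as its unguided-ACT group while the primary model still labels it a waiting list at month 8.

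What is at stake is the reading of the 6-month result. The better the unguided course works in those who take it up, the smaller the T5 difference becomes, and the more the interaction looks like loss of benefit in the ACT arm. Intention to treat and a mixed model do not remove this, because the change lies in the control condition and not in missing data or protocol deviations.

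**Working it through.** **Timeline, in months from baseline**

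- T3 = 2; T4 = 2 + 3 = 5; T5 = 2 + 6 = 8. This agrees with the stated 8 months of participation.
- Waiting-list access = 5. The course lasts 8 weeks (about 2 months), so it can end at about 7.
- T5 therefore falls about 8 − 7 = 1 month after a waiting-list participant could have finished.

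T3 precedes the offer and T4 coincides with it. Only T5 follows it.

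**The plan's own figures**

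- Drop-out step: 51 / (1 − 0.30) = 72.9, so 73 per group and 146 in total. This reproduces.
- At d = 0.50 and two-sided alpha 0.05, a two-sample t-test with 51 per group has power 0.706, not 0.80. The 0.80 level needs 64 per group two-sided, while 51 matches a one-sided test (power 0.806). That is a separate matter. It is noted here only because it explains why the single-visit reference below is 71%.

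**Inputs to the dilution check**

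- From the Sample size calculation section: 51 per arm, d = 0.50, two-sided alpha 0.05.
- Assumed: change-score SD 1, correlation 0.6 between visits, and a true guided effect of 0.50 at T3, T4 and T5 (no fading).
- Assumed: dilution x = uptake × effect of the unguided course, in SD units. For example, 50% uptake with an unguided effect of 0.20 SD gives x = 0.10.

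**Formulas**

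- T5 contrast = 0.50 − x; noncentrality = (0.50 − x) × √(51/2).
- Three-visit average = (0.50 + 0.50 + 0.50 − x)/3 = 0.50 − x/3; its variance factor is (1 + 2 × 0.6)/3 = 0.733.
- T3–T4 average = 0.50; its variance factor is (1 + 0.6)/2 = 0.80.
- Treatment-by-time: 2-df noncentral F with 2 × 51 − 3 = 99 denominator df and λ = (51/2) × (2/3)x² / (1 − 0.6) = 42.5x².

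**Results**

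| x (SD) | T5 contrast | T5 power | Three-visit average | Power of average | λ | Interaction rejects |
|---|---|---|---|---|---|---|
| 0 | 0.50 | 71% | 0.50 | 83% | 0 | 5% |
| 0.10 | 0.40 | 52% | 0.47 | 78% | 0.43 | 8% |
| 0.20 | 0.30 | 32% | 0.43 | 72% | 1.70 | 19% |
| 0.35 | 0.15 | 12% | 0.38 | 61% | 5.21 | 51% |
| 0.50 | 0.00 | 5% | 0.33 | 49–50% | 10.63 | 83% |

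The T3–T4 average has 80% power whatever x is. At x = 0.05 the three-visit average has 81%, so at very small dilution dropping T5 gains no power. The last row is an upper bound, since it needs full uptake and an unguided effect equal to the guided one. Over correlations of 0.5 to 0.7, the power of the average in that row is 46–53%.

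**The case against.** The timeline is not in dispute. The case against concerns how far the consequences reach, and most of it stands.

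- **No decisive term is named.** Primary analyses lists the fixed factors but does not say which term, contrast or visit is the primary test. With time as a factor and its interaction with treatment, the T3 and T4 contrasts are estimated separately and are largely unaffected by T5. A reader might infer that the trial's overall effect will be diluted and perhaps missed. The text supports that only if the main effect averaged over three visits is the test.
- **Uptake is unknown.** The waiting list receives an opportunity, not an assigned course. A reader might infer that the arm is mostly treated by T5, but no uptake figure supports this. Large dilution also sits poorly with the Background's premise that guidance improves effects and with the expected 30% drop-out.
- **The T5 contrast is not invalid.** Under intention to treat it remains a randomised comparison of immediate guided ACT with a wait followed by an offer of unguided ACT, and the protocol discloses the offer openly. The fault is in what the contrast is taken to estimate.
- **Responder tests have no stated visit.** They are affected only if they are run at T5.
- **This is a condensed article.** The flowchart and schedule are not shown, and the choice of decisive contrast may lie in an analysis plan.

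What remains is that the published model text itself places T5 under an ACT/WLC factor. That is a stated choice that conflicts with the Waiting list condition section, and not an omission.

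**Conclusion.** The point holds in a conditional form. As written, the T5 contrast, the T5 effect size and the part of the treatment-by-time interaction that involves T5 do not answer Objective 1, because the comparator at month 8 has had access to the course for three months. If the unguided course is taken up and helps, these quantities are pulled towards no difference, and the interaction can look like fading when nothing was lost. The distortion is zero only if nobody takes up the course or it has no effect.

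The size cannot be fixed from the documents. Over an assumed dilution of 0.10 to 0.35 SD, T5 power falls from 71% to between 52% and 12%, and the interaction test rejects in 8% to 51% of trials with no true fading. If the averaged main effect is the test, its power falls from 83% to between 78% and 61%, against 80% for T3 and T4 alone. At the low end the practical loss for the average is therefore negligible. These figures rest on a constant true d of 0.50, 51 per arm with data and a between-visit correlation of 0.6. Treating T4 as unaffected assumes that the T4 questionnaire is answered before the course is opened to the waiting list.

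**What to change.** State in Primary analyses that all ACT-versus-waiting-list inference for Objective 1 comes from T3 and T4 only. This covers treatment contrasts, the treatment-by-time test, effect sizes and responder tests. T5 data may stay in the mixed model, provided that these contrasts are defined on T3 and T4.

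Report T5 separately and label it as (i) maintenance within the ACT arm and (ii) a randomised comparison of immediate guided ACT with delayed access to unguided ACT. It should not be called ACT versus waiting list. Reporting the waiting list's uptake of the course beside the T5 results would let readers judge the dilution. The platform usage data described under Process outcomes may serve for this.

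The cost is wording only, with no new data or visits. The downside is that there will be no randomised ACT-versus-waiting-list statement at 6 months, but the design cannot support one. The protocol's moderator analysis already uses the 3-month follow-up as its indicator of treatment effect, so the change would bring the primary analysis into line with it.

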**Methods:**

A two-parallel, non-blinded randomized controlled trial (RCT) will be carried out. Adult cancer survivors who experience painful CIPN for at least 3 months and completed chemotherapy at least 6 months ago will be recruited (*n*=146). In the intervention condition, participants will follow an 8-week self-management course containing 6 modules regarding psychoeducation and ACT processes, including therapeutic email guidance. By means of text and experiential exercises, supplemented with illustrations, metaphors, and audio files, people will learn to carry out value-oriented activities in their daily life with pain. Participants will learn new ways of coping with pain, including reducing pain avoidance and increasing pain acceptance. Participants in the WLC will be invited to follow the intervention without therapeutic guidance 5 months after start. Pain interference is the primary outcome, while psychological distress, quality of life, CIPN symptom severity, pain intensity, psychological flexibility, mindfulness skills, values-based living, and pain catastrophizing will serve as secondary outcomes. All outcome measures will be evaluated at inclusion and baseline, early-intervention, mid-intervention, post-treatment, and 3- and 6-month post-treatment. Qualitative interviews will be conducted post-treatment regarding experiences, usage, usability, content fit, and satisfaction with the intervention.

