### Randomization

When the patient is admitted to the study, the patient will receive confirmation of participation, the result of randomization, and the baseline questionnaire (T0b). Patients will be randomized to receive either ACT or WLC. The study will stratify by age and sex by means of block-wise randomization. An online generator will be used for this. Randomization will be performed by a research associate.

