### Sample size calculation

Per group, 51 participants during follow-up measurements are necessary to detect minimal effect sizes of interest (*d* = .50) on the primary outcome. This is based on earlier findings on effectiveness of online and face-to-face ACT intervention for chronic pain [33, 34]. The power will be high enough (*p* = 1-beta = .80) to find significant effects in a two-sided test at alpha = .05. As found in previous online ACT interventions, a drop-out rate of 30% needs to be considered. G*Power calculations revealed that 73 participants per group are needed at baseline, which means that 146 participants are needed in total.

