#### Secondary analyses

To assess predictors of effects, steps of a study on predictors of change during CBT for chronic pain will be followed [59]. Pain interference at 3-month follow-up will be used as indicator of treatment effect. Using the PROCESS macro for SPSS [60], linear regression models will be applied (two-tailed). Predictor variables may include sex, age, educational level, number of comorbidities, time since CIPN onset, CIPN symptom severity (EORTC QLQ – CIPN20), quality of life (EORTC QLQ-C30), pain intensity (NRS), psychological distress (HADS), psychological inflexibility (PIPS), mindfulness (FMI-NL), valued based living (ELS), and pain catastrophizing (PCS). They will be selected based on theoretical and empirical considerations.

To assess differences in effects between the guided and unguided version of the intervention, independent samples t-tests and a two-stage hierarchical multiple regression analysis for each primary and secondary outcome will be conducted. Baseline to 3-month follow-up change will be used as the dependent variable. The independent variable will be an intervention dummy variable. Baseline score on the respective outcome measure will be used as control variable. Effect sizes for both conditions will be computed to indicate differences in the magnitude of the effects of online ACT with and without email counseling.

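### The primary mixed model uses change scores at T3 to T5 without the baseline score, the age and sex strata or the T1 and T2 data, and does not say which term is the test of benefit

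*Protocol article*

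**What the plan says.** The Primary analyses section of the protocol article plans an intention-to-treat analysis by general linear mixed model. The repeated measures are the differences from baseline to post-intervention (T3) and to the 3- and 6-month follow-ups (T4, T5), "with treatment (2 levels), time (3 levels) and their first-order interactions as fixed factors". No other term is listed.

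Four other places bear on this:

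- Randomization: "The study will stratify by age and sex by means of block-wise randomization".
- Secondary analyses, for guided versus unguided only: "Baseline score on the respective outcome measure will be used as control variable".
- Abstract, Methods: "All outcome measures will be evaluated at inclusion and baseline, early-intervention, mid-intervention, post-treatment, and 3- and 6-month post-treatment". Pain interference is therefore also measured at T1 (3 weeks) and T2 (6 weeks).
- Waiting list condition: participants in the control group are offered the unguided course at 5 months, which is T4.

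The Primary analyses section names imputation only for the clinical-improvement proportions. It names no primary visit or contrast.

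**The concern.** The model as stated leaves out information that the trial collects.

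- **Baseline.** An unadjusted change score fixes the slope on baseline at 1 instead of estimating it. It is less precise than the adjusted analysis whenever the correlation is below 1. The article's own guided-versus-unguided comparison makes this adjustment, so the primary comparison is analysed less efficiently than a secondary one.
- **Strata.** Age and sex are balanced by design but then left out of the listed terms.
- **Early leavers.** A participant with no score at T3, T4 or T5 has no change score and so does not enter the model, even if T1 and T2 scores exist. This sits badly with the intention-to-treat label, and it could bias the result if leaving depends on early response.
- **Which term answers Objective 1.** When the outcome is already a change from baseline, treatment-by-time no longer carries the treatment effect. Without a named contrast, it could be reported as if it did.

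**Working it through.** **1. What the outcome is.** The text speaks of differences from baseline and gives time three levels. Raw scores at T0, T3, T4 and T5 would need four levels. Three levels fit the three changes, to T3, T4 and T5.

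**2. The plan's own figure.** Inputs from the Sample size calculation section: d = .50; power .80, "to find significant effects in a two-sided test at alpha = .05"; "Per group, 51 participants during follow-up measurements are necessary"; "a drop-out rate of 30% needs to be considered".

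- Exact two-sample t-test, two-sided: 64 per group are needed. At 51 per group the power is .706.
- One-sided: 51 per group gives .806. The stated 51 is reproduced only this way.
- Dropout step: 51/(1 − .30) = 72.9, so 73 per group and 146 in total, as stated.

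The gap between .80 and .71 is a sample-size matter and is not counted here. The comparison below holds 51 per group and a two-sided 5% level fixed.

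**3. Baseline adjustment.** Take a common raw SD of 1 and baseline to follow-up correlation r.

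- Variance of the change score: 2(1 − r)
- Variance after baseline adjustment: 1 − r²
- Ratio: (1 − r²)/[2(1 − r)] = (1 + r)/2

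The article does not give r (the range .3 to .7 is assumed) and does not say which SD defines d. Both readings are shown.

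| r | 2(1−r) | 1−r² | (1+r)/2 | Power, d on raw SD: change → adjusted | Power, d on change SD: change → adjusted |
|---|---|---|---|---|---|
| .3 | 1.40 | .91 | .65 | .561 → .746 | .706 → .873 |
| .5 | 1.00 | .75 | .75 | .706 → .823 | .706 → .823 |
| .7 | .60 | .51 | .85 | .898 → .938 | .706 → .774 |

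On the raw SD, the standardised effects are .50/√[2(1−r)] and .50/√(1−r²). At r = .5 they are .50/√1.00 = .500 and .50/√.75 = .577. On the change SD they are .50 and .50/√[(1+r)/2]. At r = .5 with d on the raw SD, 80% power needs 64 per group with change scores and 49 with adjustment.

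**4. Strata.** If age and sex explain a further share R² of residual variance, the effect becomes .50/√(1 − R²). For an assumed R² of 2% to 10%, power moves from .706 to between .714 and .750.

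**5. Early leavers.** .30 × 146 = 43.8, or equivalently 146 − 2 × 51 = 44. This is a ceiling, reached only if all dropout falls before T3.

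The value of T1 and T2 was checked with illustrative patterns: 51 of 73 per group completing, missing completely at random, normal approximation, d on the raw SD. Adding T1 and T2 to a baseline-adjusted model gave about 0 to 3 points of power. With r = .5 and all dropout before T3, power went from .830 to .842 under a constant correlation. Under a correlation that decays with time, it went from .830 to .862 at T3 and stayed at .716 at T5.

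**6. The interaction.** Let δ3, δ4 and δ5 be the treatment differences in change at T3, T4 and T5. The interaction tests δ4 − δ3 = 0 and δ5 − δ3 = 0. If δ3 = δ4 = δ5 = δ, both are zero whatever the size of δ. A benefit present at T3 and fully sustained therefore gives a null interaction. The treatment term carries δ. If that term is averaged over visits, it includes T5, by when waiting-list participants may have started the course.

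**The case against.** Five points can be made in favour of the plan.

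- **The article is a summary.** A baseline covariate would not normally appear in a list of factors, and covariates may be specified in an analysis plan that is not shown. This stands as a caution. Still, the article spells out the model terms and names baseline adjustment elsewhere, so the primary model should say so too.
- **The interaction is not named as the primary test.** This stands. A reader might infer that the trial will judge benefit by treatment-by-time, but the section does not say so. It lists treatment as its own factor, which would capture a constant benefit, and it plans confidence intervals and effect sizes at each follow-up. What remains is that the decisive term is not identified.
- **Leaving out the strata does not invalidate the standard errors.** This stands. A reader might infer invalid inference. In a linear model, omitting prognostic strata tends to make standard errors too large, and omitting non-prognostic ones changes little.
- **Not everyone who drops out is lost.** This stands. Someone who leaves after T3 or T4, or who misses T3 and returns, keeps at least one change score. The 146 already allows for 30% loss, so the remaining issue is the label and possible bias.
- **The power loss depends on r and may be small.** This also stands. With d on the raw SD and r = .7 the gain is 4 points, and change scores already reach .90.

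**Conclusion.** The point holds as a matter of efficiency and clarity. The planned primary analysis is not invalid.

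The main cost comes from omitting baseline. At 51 per group, two-sided, adjustment is worth about 4 to 19 points of power over r = .3 to .7 if d is on the raw SD (.938 − .898 = .040; .746 − .561 = .185). If d is on the change SD it is worth about 7 to 17 points (.774 − .706 = .068; .873 − .706 = .167). The direction is certain for any r below 1. The size rests on an r and an SD that the article does not give.

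Including the strata brings a small gain. T1 and T2 add little power; their value is that missing-at-random becomes more plausible for people who leave before T3. The number excluded is at most about 44 of 146 and may be well below that. Treatment-by-time should not be read as the test of benefit, and the plan needs to say which quantity is.

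**What to change.** Reword the primary analysis as follows:

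- Fit one mixed model to the scores at T1, T2, T3, T4 and T5 with unstructured covariance.
- Include treatment, visit, treatment-by-visit, baseline score, baseline-by-visit, age and sex.
- Name one visit in advance, and state that the primary result is the treatment difference at that visit with its 95% confidence interval.
- Report T5 separately, because waiting-list participants may start the course at T4 and the T5 comparison is no longer against an untreated group.
- State which SD the planning value d = .50 refers to.

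The cost is slightly more analysis work and a change of wording, with no new data. The choice should be fixed before outcomes are compared by arm.

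One limit remains. The Randomization section sends the baseline questionnaire together with the allocation result, so baseline answers could be affected by knowing the allocation. Change scores share that weakness, so it is no reason to prefer them. This fix does not remove it.
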